## **5 Objectives**

The purpose of this study is to observe the impact of promoting improved complementary feeding recipes and messages developed through TIPs on children's nutritional status and identify changes in complementary feeding practices in the two districts, OtdarMeanchey and PreahVihear, in Cambodia. The overall aim of the study is to evaluate the effectiveness of the wider dissemination of improved infant and young child feeding practices developed by TIPs to improve child nutritional status. The primary objective of the study is to show that children below two years have improved Height for Age Z-scores (HAZ) after at least 18 months of complementary feeding intervention, compared to children in matched control areas. Secondary objectives are to investigate whether children in the intervention area have improved nutritional status measured by vitamin A and iron status and improved health status measured by incidence of acute respiratory infection (ARI) and diarrhea compared to children in matched control areas.

## **6 Methodology**

### **6.1 Study sites**

The intervention and control areas will be selected following the targeted area of the MALIS project in two provinces, OtdarMeanchey and PreahVihear, in Cambodia. OtdarMeanchey is divided in five districts and PreahVihear is divided in seven districts. The baseline survey will only include the target regions of MALIS.

## 6.2 Participants

Knowing that recommendations on exclusive breastfeeding are included into the behavior change strategies all households with children 0-23 months of age are eligible to participate in the surveys. During the total data assessment period, families with children with a WAZ or WHZ-score  $<-2SD$  or sick children will be send for nutrition counseling and/ or treatment according to the countries guidelines.

Inclusion and exclusion criteria for participating in the surveys are:

- being resident in the sampled area,
- having at least one child 0 – 23 month of age,
- being randomly selected,
- accepting that anthropometric measurements and blood samples will be taken.

Families with a child who does not have a written record of the child's date of birth or the date is not known by anyone in the family or who's age cannot be estimated based on a seasonal calendar of local events around one month will be excluded from the study (see chapter 6.8.3).

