### **6.7.1 Recruitment, risks and benefits**

List of possible eligible participants will be obtained from official population's list.

There is no risk to the participants involved in the study.

**Benefits to Participants:** This study has an indirect benefit to the participants. The study does provide an opportunity for the participants to gain information about their and their children's current nutritional and health status. Participants will receive a "Participants-Card" including their and their children's health data available directly in the field (anthropometric data, age and hemoglobin level). The card will provide information whether the anthropometric measurements or the measured hemoglobin level indicate poor nutritional status. In case of abnormal results participants will be sent for nutrition counseling/ or treatment according to the guidelines of Cambodia for treatment of anemia and malnutrition.

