## 10.3 Participants Card

| Women 18-45 years:      |                       |
|-------------------------|-----------------------|
| Hemoglobin (Hb, g/dl)   |                       |
| < 8                     | Severe anaemic        |
| < 11                    | Anaemic               |
| 12                      | Normal (non-pregnant) |
| 11                      | Normal (pregnant)     |
| BMI                     |                       |
| < 18.5                  | Underweight           |
| 19 – 25                 | Normal                |
| 25 – 30                 | Overweight            |
| > 30                    | Obese                 |
| Children under 2 years: |                       |
| WAZ                     | HAZ                   |
| 0                       | 0                     |
| <-2                     | <-2                   |
| <-3                     | <-3                   |
| Children 6-23 months:   |                       |
| Hemoglobin (Hb, g/dl)   |                       |
| < 7                     | Severe anaemic        |
| < 11                    | Anaemic               |
| ≥                       | Normal                |

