### Results of anthropometry and hemoglobin

|        | Height (cm)          | Weight (kg)          | BMI (kg/m  ) | Hb (g/dl)            |
|--------|----------------------|----------------------|--------------------------|----------------------|
| Mother |  |  |      |  |
| Father |  |  |      |  |

| Age of child (months) | Height (cm)          | Weight (kg)          | WAZ                  | HAZ                  |
|-----------------------|----------------------|----------------------|----------------------|----------------------|
|   |  |  |  |  |

Edema: no ☐ yes ☐ Hb (g/dl)

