### Conclusion

Nutritional status of mother alarming? no ☐ yes ☐

Nutritional status of child alarming? no ☐ yes ☐

→ If yes, please contact the next health post

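### The Participants Card (annex 10.3) lists WAZ and HAZ but not WHZ, one of the two anthropometric indices on which section 6.2 refers a child

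*Protocol*

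**What the plan says.** Three places in the protocol bear on this.

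- **Section 6.2 (Participants)** sets the referral rule for the whole period of data collection. It covers "families with children with a WAZ or WHZ-score" below -2 SD, and sick children. These families are to be sent for nutrition counselling, treatment or both.
- **Section 6.7.1 (Recruitment, risks and benefits)** describes the Participants Card as a benefit to families: "The card will provide information whether the anthropometric measurements or the measured hemoglobin level indicate poor nutritional status". A separate sentence adds a general rule: "In case of abnormal results participants will be sent for nutrition counseling/ or treatment". No z-score is named there.
- **Annex 10.3 (Participants Card)** gives the card itself. The cut-off table headed "Children under 2 years" has a WAZ column and an HAZ column, each with the entries 0, below -2 and below -3. The row of child result fields that opens with "Age of child (months" continues with height, weight, WAZ and HAZ; edema and hemoglobin follow below. The card closes by asking "Nutritional status of child alarming" and, for a yes, tells the family: "If yes, please contact the next health post".

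Section 6.8.2 provides for weight and recumbent length to be taken from every child.

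**The concern.** The referral rule and the form that reports results to the family use different sets of indices. WHZ is a trigger in its own right under 6.2, because the two indices are joined by *or*. Yet the card has no space to record it and no cut-off to compare it with. WHZ is named nowhere else in the protocol text available, so no other section supplies the missing link.

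What is at stake is care of the individual child. WHZ is the index of low weight relative to length. A family whose child is low on that index alone would hold a card on which nothing weight-based looks low, although the protocol says the child should be referred. Section 2.2 describes wasting in Cambodia as more common than in neighbouring countries, so the index is relevant in this population.

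**Working it through.** No formula applies. The check sets the two index lists side by side.

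**Inputs**

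- Anthropometric triggers in section 6.2: WAZ, WHZ.
- Z-scores in the card's child cut-off table (annex 10.3): WAZ, HAZ.
- Z-scores in the card's child result fields (annex 10.3): WAZ, HAZ.

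**Comparison**

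The only index common to both lists is WAZ. So 1 of the 2 referral indices in 6.2 appears on the card, and WHZ appears in 0 of the 2 legible child tables. HAZ is on the card without being a 6.2 trigger. That is not a fault: HAZ is the primary outcome, the family is entitled to see it, and the general rule in 6.7.1 can cover it.

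**What this means for each type of child**

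| WAZ | WHZ | Referral under 6.2? | Low weight-based z-score on card? |
|---|---|---|---|
| below -2 | below -2 | yes | yes (WAZ) |
| below -2 | -2 or above | yes | yes (WAZ) |
| -2 or above | below -2 | **yes** | **no** |
| -2 or above | -2 or above | no (unless sick) | no |

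Only the third row is discordant. In the second row the child is already shown as low through WAZ.

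**Can the gap be closed with data already taken?** Yes. WHZ is derived from weight and length. Section 6.8.2 collects both, and the card already has fields for height and weight.

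**How many children fall in the third row?** The protocol gives neither a wasting prevalence nor any joint distribution of WAZ and WHZ. The number cannot be derived, and none is offered here.

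**The case against.** The strongest reply is that the two texts do different jobs. Section 6.2 places a duty on the study team. The card is an information sheet for the family. Nothing says that staff refer from the card, or only on what it prints. By making WHZ a trigger during data collection, 6.2 already implies that the team will derive it in the field. Other routes also exist: sick children are referred, edema is tested and recorded, and 6.7.1 refers on any abnormal result. In a population as short as the one assumed in section 6.4 (control mean HAZ -1.96), many children with low WHZ may be low on WAZ too, which would keep the discordant group small.

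Most of this stands. A reader might infer that children low on WHZ alone will go without referral. The documents do not support that, because the 6.2 duty holds whatever the card prints.

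A reader might also infer that the closing question on the card has no criterion behind it. That is not supported either. The copy available for review is incomplete next to this part of the card, and the z-score rows have no labels where the hemoglobin and BMI rows do, so a key may have been lost. The printed cut-offs may well be meant to inform that box.

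What the reply does not remove is the mismatch itself. Section 6.7.1 says the card will report whether the anthropometry indicates poor status, and for one of the protocol's own two indices it cannot. The z-score columns are legible in both child tables, so this narrower point does not depend on the damaged part.

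**Conclusion.** The point holds in a limited form: the card, as far as it is legible, omits WHZ and so cannot show one of the two anthropometric referral indices in 6.2. It is a cheap improvement for participant safety, of minor weight.

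The conclusion rests on two assumptions. The first is that the legible cut-off table and result fields list all the z-scores on the card. The second is that *or* in 6.2 means either index suffices.

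No count of affected children can be attached to it. Nor should it be read as bearing on the trial's results: the comparison of mean HAZ, the sample size and the power do not depend on what the card displays.

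**What to change.** Add a WHZ result field to the child row of the Participants Card, and a WHZ column with -2 and -3 cut-offs to its child table, in the same form as WAZ and HAZ. Derive the value from the weight and length already taken under section 6.8.2. A child low on WHZ alone is then flagged on the card in line with section 6.2.

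The cost is a reprinted card and one more z-score lookup per child in the field. No new measurement is needed.

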## **1 Abstract**

Undernutrition remains one of the biggest challenges in developing countries. Children aged 0-23 months are the most vulnerable group with a peak incidence of mortality and morbidity. The Cambodian Demographic and Health Survey 2010 estimated a national stunting prevalence of 40%. Results show that stunting increases after six months of age when most children receive complementary feeding. The promotion of a nutrient-dense diet based on locally available foods is essential to improve the nutritional status of young children. In order to optimize infants and young children's diets, the FAO project "Improving food security and Market Linkages for Smallholders in Otdar Meanchey and Preah Vihear Provinces (MALIS)" will implement a food security project with a nutrition education component.

The objective of the research is to evaluate the effectiveness of the behavior change messages which will be delivered through a community based intervention involving community based organizations. The research design encompasses both qualitative and quantitative methods, including two cross-sectional surveys, focus group discussions and key informant interviews. The first cross-sectional survey will take place prior to the intervention to assess the baseline nutrition security situation of families with children below two years in the MALIS project region. The behavior change communication strategies will be implemented in the prior selected intervention areas by the MALIS project. The second cross-sectional survey will be conducted after at least 18 months of intervention evaluating the impact of the intervention by a research team.

The primary outcome parameter to be measured will be mean Height for Age z-Scores (HAZ). Secondary outcome parameters will be vitamin A deficiency, iron deficiency and behavior change. Methods for data collection will include anthropometric measurements, questionnaires, collection of blood plasma by finger prick and focus group discussions. Statistical analysis will compare primarily the difference of the mean height-for-age z-score of children in intervention and control areas.

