## 6.5 Randomization procedure

A simple randomization proportional to population per district will be conducted to select 75 survey villages for the baseline. In each village 15 households with children under two will be randomly selected. In case there are less than 15 households with children under two in the selected village, the missing number of households will be randomly selected from the closest neighbouring village. The intervention and control villages are assigned following a restricted randomization based on the results of the baseline survey.

This implies that randomization will take place after adjusting for certain variables that might interfere with variables of interest to the study. Variables of adjustment are:

- district officer
- level of stunting
- total village population
- average land holding size
- wealth status
- access to health posts, nutrition rehabilitation unit, or nutrition counseling by a NGO

The selected clusters will be the objective of randomization. Randomization will be done using the Software package “Experiment” and the operation “randomize”. The “Experiment”-package is a software extension to the statistical software  $R^{\circledast}$ . It serves to design and analyze different types of randomized trials, including cluster randomized trials, block, or matched pair designed trials (60). The baseline and the impact survey will randomly select the study participants in the selected clusters.

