### **6.7.2 Informed consent**

Prior to the surveys, general consent of the EU FAO project communities to participate in this trial will be obtained. Written consent will be obtained by the individual household to be interviewed at the day of data assessment.

The Investigators will be responsible for ensuring informed consent is obtained before any protocol specific procedures are carried out. The decision of a participant to participate in the research study is voluntary and will be based on a clear understanding of what is involved. Participants will receive adequate oral and written information about the nature and purpose of the study, participation/termination conditions, and risks and benefits – appropriate Participant Information and Informed Consent Forms are provided in the Annex. The oral explanation to the participants will be performed by designated people (enumerators), and must cover all the elements specified in the Participant Information Sheet and Informed Consent Form.

The participants will be given every opportunity to clarify any points they do not understand and, if necessary, ask for more information. The participant will be given sufficient time to consider the information provided.

The enumerator and the participant have to sign and date the Informed Consent Form to confirm that consent has been obtained. The participant will be provided with a copy of this document.

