## **6.8 Data collection**

The data collection in the cross sectional surveys will be based on an adaptation of the SMART methodology (49). The SMART methodology includes a questionnaire designed to assess mortality, nutritional status and food security in crisis situations. The final questionnaire will consist of standardized modules extracted from the questions designed by the SMART initiative, FAO, WHO, GIZ, and the Manoff Group (1, 6, 49, 54,55-59). Thus, mothers/caretakers with children below two years will be interviewed about their socio-economic situation, food security, mothers' and children's food intake, care, time availability, access to health, water and sanitation, motor milestones, and access to FAO food security activities by trained enumerators. Anthropometric measurements will be taken from mothers, their children below two years of age, and, if possible from fathers, by a nutritionist especially trained in anthropometric measurements. Capillary blood samples will be taken from the surveyed mothers (Hb only) and children below two years to assess the micronutrient status (retinol binding protein (RBP), transferrin receptor (TfR), hemoglobin as well as the morbidity status (C-reactive protein (CRP), acyl glycoprotein (AGP) by medical trained research staff.

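### Acceptance of blood sampling is a condition of survey entry, so families who refuse only the finger prick are needlessly lost from the primary HAZ comparison

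*Protocol*

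**What the plan says.** Protocol section 6.2 opens its list with "Inclusion and exclusion criteria for participating in the surveys are" and ends it with "accepting that anthropometric measurements and blood samples will be taken". The two procedures are joined, no exception is given for declining blood alone, and the list applies to the baseline and the impact survey alike.

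The abstract and section 5 make mean HAZ the primary outcome. Blood supports secondary outcomes only: "Secondary outcome parameters will be vitamin A deficiency, iron deficiency and behavior change", of which behaviour change needs no blood. Section 6.8 widens the blood requirement beyond the child: "Capillary blood samples will be taken from the surveyed mothers (Hb only) and children below two years".

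On timing, section 6.5 states: "The intervention and control villages are assigned following a restricted randomization based on the results of the baseline survey". It also states: "The baseline and the impact survey will randomly select the study participants in the selected clusters". Section 6.7.2 adds: "Written consent will be obtained by the individual household to be interviewed at the day of data assessment". At the impact survey, individual consent therefore comes after allocation and, under section 6.3.2, after at least 18 months of intervention.

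The only provision for refusal is the 10% that section 6.4 adds for drop-out and non-response together. The logical framework in annex 10.1 lists full participation and absence of refusal as assumptions.

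**The concern.** HAZ is computed from length, age and sex. The dietary diversity, knowledge, respiratory infection and diarrhoea outcomes in section 4 come from the interview. None of these needs a blood sample, yet all are lost for a family that declines the prick.

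Two things are at stake. The first is number: usable primary-outcome data are given up for the sake of a secondary measurement. The second is comparability: at the impact survey, entry to the primary comparison depends partly on a choice made after allocation about a procedure that has no bearing on HAZ. If that choice were related both to arm and to HAZ, the estimated difference would be biased, and a larger sample would not remove the bias. The 10% allowance protects the sample size but not the balance between arms.

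**Working it through.** **Inputs (Protocol section 6.4).** SDs 1.5 and 1.2, so the variance sum is 2.25 + 1.44 = 3.69; 80% power; 95% confidence, two-sided; a 15% change from −1.96, so δ = 0.15 × 1.96 = 0.294; ICC 0.03; 19 children per village; 10% added for non-response. The document gives no refusal rate, no arm difference in refusal and no HAZ gap for refusers, so all such values below are assumptions.

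**Reproducing the plan's figure.**
- n = (1.96 + 0.842)² × 3.69 / 0.294² = 7.849 × 3.69 / 0.0864 = 335 per arm. (The printed rounded means, with δ = 0.30, would give 322.)
- DEFF = 1 + 0.03 × 18 = 1.54; 335 × 1.54 = 516.
- 516 × 1.10 = 567.6, rounded to 568.

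**Power under loss.** Power = Φ(δ/SE − 1.96), with SE = √(3.69 × DEFF / n).
- All 568 measured: SE 0.100, power 83.6%.
- Total loss of 10%, blood refusal included: n = 511, power 79.6% at DEFF 1.54. If the number of villages is fixed at 568/19 ≈ 29.9 per arm, cluster size falls to 17.1, DEFF to 1.483, and power is 81.1%.
- The non-response allowance already used (n = 516) and a further 10% refusing blood: n = 464. This is an 18% loss from 568.
- The same with a further 20%: n = 413, a 27% loss from 568.

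| Refusal beyond the allowance | DEFF held at 1.54 | 27.2 villages per arm (516/19) | 29.9 villages per arm (568/19) |
|---|---|---|---|
| 10% | 75.7% | 77.3% (DEFF 1.483) | 78.6% (DEFF 1.436) |
| 20% | 70.7% | 74.0% (DEFF 1.426) | 75.3% (DEFF 1.384) |

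The last two columns keep villages fixed, so that DEFF falls with cluster size.

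**Bias under differential refusal.** If acceptors exceed refusers by a gap g in both arms, the acceptors' mean exceeds the arm's true mean by r × g, where r is the refusal rate. The bias in the arm difference is therefore (r₁ − r₀) × g.
- Example: r = 5% in intervention and 15% in control villages, g = 0.3. Size: 0.10 × 0.3 = 0.03 HAZ, and 0.03/0.294 = 10% of the planned difference. The sign depends on which arm refuses more and on whether refusers are shorter or taller.
- Against the SE at 516 per arm (0.105): 0.03/0.105 = 0.29.
- Wider range: gaps of 0.25 to 1.0 with arm differences of 5 to 15 points give 0.0125 to 0.15 HAZ, or 4% to 51% of 0.294.
- With equal refusal and the same gap in both arms, the bias is zero.

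**The case against.** The strongest reply is that the arm difference in refusal is conjecture. A reader might infer that control villages know their status, or that families are more willing where the project works, and hence that the HAZ comparison is biased. The protocol does not support this. No section says that control villages are told their allocation. Section 6.1 selects both intervention and control areas following the MALIS target area, so project presence may not separate the arms; annex 10.1 refers to non-project areas, so the point is unsettled. Surveyed villages meet the finger prick at baseline, before allocation, and section 6.7.1 offers the same haemoglobin result and referral to all participants. This part of the objection stands.

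A reader might also infer that power necessarily drops to 76% or 71%. Those values need the whole 10% allowance to be spent on other causes and DEFF to stay at 1.54 while villages shrink. A repeated cross-sectional survey has few drop-outs, so refusal at consent is largely what the allowance is for. That stands too, and is why ranges are given.

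Two further points are fair. Requiring every core measurement, so that growth and blood results come from one sample, is a recognisable design choice. And the consent form is not available here, so a partial-consent option cannot be excluded; the participant checklist in the annexes already ticks interview, anthropometry and each blood test separately. If the form does allow partial consent, however, it conflicts with section 6.2 and the two need reconciling. Nothing in the objection shows that a family declining only blood stays in the HAZ analysis.

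**Conclusion.** The point holds as a needless exclusion. Section 6.2 makes blood acceptance a condition of entry, HAZ does not need it, and no visible text reverses this. The criterion also leaves open a post-allocation selection route that could be closed at little cost. Whether refusal would differ by arm, in which direction and by how much cannot be learned from the protocol, and it should not be reported as a demonstrated bias.

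The likely size is modest. Power stays close to 80% if total non-response is near 10%, and falls to the 70s only if blood refusal comes on top of that. The illustrative bias is under 0.3 of a standard error, and it becomes material only if refusal differs clearly by arm and refusers differ markedly in HAZ. Confidence is high on the wording and its consequence for eligibility, and low on the magnitude. Severity is minor to moderate.

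**What to change.** In section 6.2, limit the entry criterion to interview and anthropometric measurement. Take separate, optional consent for blood, covering the mother's and the child's samples, and bring the consent form into line. Keep families who decline blood in the HAZ and interview-based analyses; analyse anaemia and RBP among those with samples. Record blood refusal by village and report it by arm.

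The cost is one edited criterion, plus a separate consent item if the form lacks one. The sample-size figures of 335, 516 and 568 do not change. The downsides are that some measured children will have no blood result and that blood uptake may fall slightly once it is optional. The change does not deal with refusal of the interview or of anthropometry after allocation; that exposure comes from sampling afresh in allocated villages and remains.
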